#### Efficacy secondary outcomes (study population is given in brackets)

7.Normalized cumulative fluid balance measured in both groups at H24 and H72 after inclusion or death, whichever comes first, and at day 7 in alive patients. Fluid balance measured between inclusion and early time point (H24 or H72 or death) will be normalized by dividing it by the observation period duration and expressed in ml h^−1^. The fluid balance at H24 and H72 will be quantified using the same input and output items as per the primary outcome. The fluid balance at day 7 will be estimated based on the change in body weight between inclusion and day 7 [*ITT population*].8.Normalized cumulative UF_NET_ volume in both study groups at H24 and H72 after inclusion or death, whichever comes first. Cumulative UF_NET_ measured between inclusion and H24 or H72 or death will be normalized by dividing it by the observation period duration and expressed in ml h^−1^. The cumulative UF_NET_ volume will be computed based on the UF_NET_ volumes reported every 4 h between inclusion and 24 or 72 h after inclusion or death, whichever comes first [*ITT population*].9.PaO_2_ to FiO_2_ ratio and the extravascular lung water index measured with the cardiac output monitoring device, measured once a day from inclusion to H72 or death, whichever comes first. The FiO_2_ is the FiO_2_ set on the respirator or the high-flow nasal cannula device. In non-ventilated patients, the FiO_2_ will be estimated using the following formula: FiO_2_ = 0.21 + 0.03 × oxygen flow rate (in L min^−1^) [25] [*ITT population*].10.The number of ventilator-free days in both study groups, quantified as the number of days alive without mechanical ventilation, starting at the time of inclusion and censored at day 28 of inclusion. Mechanical ventilation weaning will be defined if invasive mechanical ventilation is not required for a continuous period of 48 hours or longer. A value of 0 is allocated if the patients died between inclusion and day 28. A value of 0 is also allocated if the patient is still receiving invasive mechanical ventilation at day 28 [24]. In case of multiple mechanical ventilation weaning episodes, only the last weaning attempt will be considered [*ITT population*].11.MAKE-90 assessed between inclusion and day 90 after inclusion in both groups. MAKE-90 comprises death before or at day 90, RRT dependence at day 90, and persistent stage 2 or 3 acute kidney injury (as per the KDIGO guidelines) at day 90. RRT dependence is present if the patient is still receiving CRRT at day 90 or if he has received an intermittent technique in the time frame of ±2 days around day 90. Persistent acute kidney injury is adjudicated based on a baseline plasma creatinine concentration (identified in the 6 months to 7 days before ICU admission), and the plasma creatinine measured at day 90 [6]. In case of missing baseline creatinine value, it will be retrospectively estimated [26]. Each element of the composite event will be evaluated separately [*ITT population*].12.Hospital and ICU length of stay, quantified as the duration, in days, between inclusion and hospital and ICU discharge (alive or deceased), respectively [*ITT population*].

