#### Efficacy secondary objectives

7.To assess the impact of the intervention strategy on the cumulative fluid balance (normalized to the observation period) over the first 24 h, 72 h, and 7 days following inclusion, respectively, as compared to the control strategy8.To assess the impact of the intervention strategy on the cumulative net ultrafiltration (normalized to the observation period) over the first 24 h and 72 h following inclusion, respectively, as compared to the control strategy9.To evaluate the effectiveness of the intervention to prevent or limit fluid overload-related hypoxemic respiratory failure, by comparing the arterial O_2_ partial pressure (PaO_2_) to O_2_ inspired fraction (FiO_2_) ratio on the one side, and the extravascular lung water index on the other, in the two study groups, between inclusion and H72 after inclusion10.To evaluate the impact of the intervention strategy on ventilatory-free days at day 28 of study participation, by comparing the number of days alive without mechanical ventilation in the two study groups and censored at day 28 of participation11.To evaluate the effect of the intervention strategy on long-term renal outcome, by comparing the rate of the composite outcome of major adverse kidney event (MAKE) evaluated at day 90 of inclusion in the two study groups. MAKE-90 comprises death, RRT dependence, or persistent stage 2 or 3 acute kidney injury at day 90 of inclusion [6]12.To assess the ability of the intervention strategy to decrease hospital and intensive care length of stay, as compared to the control strategy

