
#### Feasibility secondary outcomes (study population is given in brackets)

13.The number of eligible patients per month and per participating center and the number of patients effectively enrolled in the trial per month and per participating center. [N/A]

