### Sample size {14}

We make the hypothesis that the fluid balance will be of 4000 ± 4000 ml at H72 of inclusion in the control group and that the intervention strategy will generate a fluid balance of 0 ± 4000 ml at H72 of inclusion (absolute between groups difference of 4000 ml). The hypothesis is based on the data reported by a large randomized controlled trial evaluating the timing of RRT in the ICU, in which the H72 cumulative fluid balance was 3711 ml in the early arm and 3917 ml in the delayed arm of the study [18]. Based on this hypothesis, the required sample size to compare two means between two equally sized samples (and a bilateral hypothesis), with a *⍺* of 0.05 and a power 1–*β* of 0.8, would be 16 patients per arm, hence a total of 32 patients. Since (1) we expect a non-survival rate of 25% at 72 h of inclusion (corresponding to the time point of the primary outcome evaluation) and (2) the expected distribution of the primary outcome would not follow the normal distribution, justifying an increase of 25% in sample size, the final total number of patients to enroll would be 58, equally distributed between study groups. Patients deceased before 72 h of inclusion, or alive at H72 but with a missing primary outcome measure, will not be included in the analysis of the primary outcome. Once the required number of 21 patients per arm with an assessable primary outcome will be reached, inclusions will cease.

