#### Analysis of the secondary outcomes

All secondary outcome measures will be analyzed in the ITT population (see section for definition). The following outcomes will be reported with median and interquartile range (with minimum and maximum values) in each study group and compared between the groups using Mann-Whitney’s test:Vasopressor-free day (secondary outcome #4)Normalized cumulative fluid balance (secondary outcome #7)Normalized cumulative UF_NET_ (secondary outcome #8)Ventilator-free day (secondary outcome #10)Hospital/ICU length of stay (secondary outcomes #12)

The secondary outcomes listed below will be reported longitudinally over time (from inclusion to H72) in the ITT population and compared between the study groups using mixed effects regression models with a fixed interaction of group by time, and a random effect with the patient identifier to account for the repetition of measurements, as well as an offset accounting for baseline values. In case of a significant interaction, a post hoc multiple comparison analysis between study groups will be performed, adjusted for the repetition of tests by the Tukey method.Number of hemodynamic instability episodes (secondary outcome #1)Number of hemodynamic instability episodes with preload dependence (secondary outcome #2)Hemodynamic parameters (secondary outcome #3)Total SOFA score and hemodynamic SOFA score (secondary outcome #5)PaO_2_/FiO_2_ ratio and extravascular lung water index (secondary outcomes #9)

The following categorical outcomes will be reported with count and percentage in each study group and compared between groups using the chi-squared or Fisher exact test: severe adverse events and adverse events of special interest, vital status (secondary outcome #6), and MAKE-90 (secondary outcome #11). Finally, no statistical test will be performed with secondary outcome #12. The hemodynamic profiles identified by the hemodynamic protocol of the intervention group will be reported in the supplemental results of the study.

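### Length of stay (secondary outcome #12) ends at death as if at discharge, so early deaths receive favourable ranks in a comparison where shorter is better

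*Protocol article*

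**What the plan says.** Under Efficacy secondary objectives, the aim for this outcome is "To assess the ability of the intervention strategy to decrease hospital and intensive care length of stay, as compared to the control strategy". A shorter stay is thus the sought effect.

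Under Efficacy secondary outcomes, the outcome is defined as "Hospital and ICU length of stay, quantified as the duration, in days, between inclusion and hospital and ICU discharge (alive or deceased), respectively", in the intention-to-treat population. No separate rule for deaths is given. In the same section, ventilator-free days carry one: "A value of 0 is allocated if the patients died between inclusion and day 28". Vasopressor-free days (#4, Safety secondary outcomes) carry the same rule.

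Analysis of the secondary outcomes includes the entry "Hospital/ICU length of stay (secondary outcomes #12" in the list compared by Mann-Whitney. The last paragraph of that section then says: "Finally, no statistical test will be performed with secondary outcome #12".

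On expected early mortality, Sample size {14} states "we expect a non-survival rate of 25% at 72 h of inclusion".

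**The concern.** Mann-Whitney uses only the order of the values. If the stay of a patient who dies on day 1 is recorded as one day, that patient outranks nearly every survivor on an outcome where low is good. Two outcomes in the same plan (#4 and #10) put death at the unfavourable end; #12 puts it near the favourable end, and the article gives no reason for the difference.

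At stake is the meaning of the comparison. A difference in stay could reflect faster recovery or more early deaths, and the test cannot tell them apart. With a quarter of patients expected to die within three days, the deaths are too many to ignore.

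A smaller matter is that the analysis section gives two instructions for #12, one to test it and one not to.

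**Working it through.** **1. The plan's own figures.** The article gives no figure for length of stay. The number per arm comes from Sample size {14}: 2 × (1.96 + 0.84)² × (4000/4000)² = 15.7, rounded up to 16 per arm. Dividing by 0.75 twice gives 16/0.75/0.75 = 28.4, rounded up to 29 per arm, 58 in total. The stated 58 reproduces, and 29 per arm is used below.

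**2. Direction, in closed form.** Let p0 and p1 be mortality before discharge in the two arms. Survivors' stay S has the same distribution in both arms, and so has time to death D. Let q = P(D < S). Two deaths, or two survivors, contribute ½ each, so

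P(arm 1 stay < arm 0 stay) = ½[p0·p1 + (1−p0)(1−p1)] + p1(1−p0)q + p0(1−p1)(1−q) = ½ + (p1 − p0)(q − ½).

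If deaths mostly come sooner than discharges alive (q > ½), higher mortality in arm 1 makes arm 1 look better. The shift is at most half the mortality excess. If deaths are tied at the worst rank, q becomes 0 and the expression is ½ − (p1 − p0)/2, so the direction reverses.

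**3. Size, with assumed inputs.** Survivor stay is gamma with mean 20 days and shape k; time to death is exponential with mean 8 days; control mortality is 40%. Then q = 1 − (1 + (20/k)/8)^(−k), which is 0.714, 0.802 and 0.857 for k = 1, 2 and 4.

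| Mortality excess | As written, k = 1 / 2 / 4 | Deaths ranked worst |
|---|---|---|
| 5 points | 0.511 / 0.515 / 0.518 | 0.475 |
| 10 points | 0.521 / 0.530 / 0.536 | 0.450 |
| 20 points | 0.543 / 0.560 / 0.571 | 0.400 |

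For k = 2 and 40% v 60% mortality, median stay is 11.6 v 9.1 days, the shorter being in the higher-mortality arm.

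**4. Chance of a falsely significant result.** Simulation with 29 per arm, k = 2 and a two-sided Mann-Whitney test at 0.05 gives a significantly shorter stay in the higher-mortality arm in about 4% of trials (5 points), 5 to 6% (10 points) and 11 to 12% (20 points). With equal mortality it is about 2.3%. With deaths ranked worst it is about 1% or less throughout.

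**5. Sensitivity to the 72 h figure.** The model in step 3 puts only 0.40 × (1 − e^(−3/8)) = 12.5% of controls, and 0.60 × 0.313 = 19% of the other arm, dead by 72 h, below the protocol's 25%. An alternative fixes control mortality at 25% by 72 h, with those deaths between days 0.2 and 3, all other stays at least 3 days, survivor stay lognormal with median 20 days, and 0 to 25% later control deaths. Here early deaths precede every other stay, so the probability is ½ + 0.10 × ½ = 0.55 for 35% v 25% and 0.60 for 45% v 25%. A falsely significant shorter stay then appears in about 9 to 10% and 24 to 27% of trials, against 2 to 2.5% with equal mortality. With deaths ranked worst it falls to about 0.2 to 1.1%, and to 0.1% or less.

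**6. The two instructions for #12.** The analysis section assigns #4, #7, #8, #10 and #12 to Mann-Whitney; #1, #2, #3, #5 and #9 to mixed models; #6 and #11 to chi-squared or Fisher. Only the feasibility outcome, "13.The number of eligible patients per month and per participating center", has no method, and a closing no-test sentence fits it.

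**The case against.** The best defence is that the definition is open and unambiguous, and that mortality stands beside it. Vital status at H72, day 28 and day 90 is compared between groups (#6), death is a component of MAKE-90 with each element evaluated separately (#11), death is an adverse event of special interest, and 72 h mortality has an interim safety look. A shorter stay caused by deaths would be published with its explanation. #12 is also one of thirteen secondary outcomes in a 58-patient trial with a physiological primary outcome. Finally, the illustrated effects need a mortality excess with no change in survivors' stay, and for excesses of 5 to 10 points the distortion is small (0.51 to 0.54).

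Most of this stands as mitigation. It limits the harm and the priority, but it does not make the #12 comparison interpretable: mortality reported elsewhere does not show how much of a difference in stay is due to it.

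Three stronger readings are tempting, and the documents support none of them:

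- A reader might infer that the intervention is expected to raise mortality. Nothing in the article says so; the excess is assumed only to show direction.
- A reader might infer that the plan forbids testing #12. The two sentences conflict literally, but the count of assigned outcomes points to a numbering slip for #13.
- A reader might infer that the choice is left open until after unblinding. The trial is open-label with no unblinding procedure, and analysts are to be blinded to group, though the article concedes that allocation may be deduced. The fair statement is that the choice should be fixed before database lock.

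**Conclusion.** The concern holds as a fault in the scoring of one secondary outcome. The rule for deaths is stated in the article, not left out of it, and it ranks early death as a favourable result, contrary to #4 and #10. The direction follows from the definition, provided that deaths tend to come sooner than discharges alive, which the expected 25% mortality by 72 h makes likely.

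The size is assumption-driven. It rests on identical survivor stay in both arms and on the assumed distributions and mortality excess. For a 5- to 20-point excess the distortion is modest at the lower end and material at the upper end. The larger false-positive rates in the sensitivity check require a 20-point excess in 72 h mortality, for which the article gives no basis. The primary outcome and the sample size are unaffected. The change should be made, but the trial's main conclusion does not hang on it. The conflicting sentences on #12 need only an editorial correction.

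**What to change.** Before database lock, state one rule for #12:

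- keep Mann-Whitney and give patients who die before the discharge in question the worst rank, in line with #4 and #10; or
- analyse time to discharge alive with death as a competing event (cumulative incidence, for example with Gray's test).

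In either case, report stay in survivors and non-survivors descriptively.

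Separately, change #12 to #13 in the closing no-test sentence of Analysis of the secondary outcomes.

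The cost is about two sentences. Discharge dates and vital status are already needed for #12 and #6. The price in interpretation is that the outcome becomes a composite of stay and survival and no longer measures resource use alone; the descriptive split by survival status keeps that information available.

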
#### Feasibility secondary outcomes (study population is given in brackets)

13.The number of eligible patients per month and per participating center and the number of patients effectively enrolled in the trial per month and per participating center. [N/A]

### Participant timeline {13}

Participants’ timeline is shown in SM3, Supplemental Fig. 3, and the exact steps prior to and during enrollment are given in SM3, Supplemental Table 2.

### Sample size {14}

We make the hypothesis that the fluid balance will be of 4000 ± 4000 ml at H72 of inclusion in the control group and that the intervention strategy will generate a fluid balance of 0 ± 4000 ml at H72 of inclusion (absolute between groups difference of 4000 ml). The hypothesis is based on the data reported by a large randomized controlled trial evaluating the timing of RRT in the ICU, in which the H72 cumulative fluid balance was 3711 ml in the early arm and 3917 ml in the delayed arm of the study [18]. Based on this hypothesis, the required sample size to compare two means between two equally sized samples (and a bilateral hypothesis), with a *⍺* of 0.05 and a power 1–*β* of 0.8, would be 16 patients per arm, hence a total of 32 patients. Since (1) we expect a non-survival rate of 25% at 72 h of inclusion (corresponding to the time point of the primary outcome evaluation) and (2) the expected distribution of the primary outcome would not follow the normal distribution, justifying an increase of 25% in sample size, the final total number of patients to enroll would be 58, equally distributed between study groups. Patients deceased before 72 h of inclusion, or alive at H72 but with a missing primary outcome measure, will not be included in the analysis of the primary outcome. Once the required number of 21 patients per arm with an assessable primary outcome will be reached, inclusions will cease.

### Recruitment {15}

The participating ICUs are dedicated to the care of severely ill patients such as those fulfilling the inclusion criterion. All have experience in advanced hemodynamic monitoring, used in routine care by the nursing staff. The application of the hemodynamic assessment and determination of profiles takes less than 5 min every 4 h. Also, in an observational study assessing the causes of hypotension in critically ill patients requiring CRRT, the enrollment rate of the coordinating center was between 1 and 2 per month over the study period (12 to 24 enrolled patients per year) [9].

In order to achieve recruitment, all the clinicians of the participating ICU will receive a detailed information about the study. All patients treated with CRRT will be screened daily to evaluate study eligibility. To ensure an adequate number of participants will be enrolled in the required time frame, the participating centers will be asked to report on a regular basis their problems related to enrollment, in order to find adequate responses to improve the enrollment rate. Additional centers will be sought in case the enrollment rate in the trial is too low. Finally, a 1-year extension of the study time frame will be proposed in case the enrollment rate in the trial is too low.

## Assignment of interventions: allocation

### Sequence generation {16a}

Allocation sequence will be computer-generated with stratification based on the fluid overload status at the time of enrollment. Fluid overload will be defined as a 10% increase in body weight between ICU admission and trial enrollment [2]. Fluid overload is a known risk factor for ICU mortality. Randomization will be performed in each stratum, with a 1:1 ratio, and using a fixed block size. The block size will only be known by the statistician in charge of the randomization list.

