**Methods:**

The GO NEUTRAL trial is a multicenter, open-labeled, randomized, controlled, superiority trial with parallel groups and balanced randomization with a 1:1 ratio. The trial will enroll adult patients with acute circulatory failure treated with vasopressors and severe acute kidney injury requiring CRRT who already have been equipped with a continuous cardiac output monitoring device. After informed consent, patients will be randomized into two groups. The control group will receive protocolized fluid removal with an UF_NET_ rate set to 0–25 ml h^−1^ between inclusion and H72 of inclusion. The intervention group will be treated with an UF_NET_ rate set on the CRRT of at least 100 ml h^−1^ between inclusion and H72 of inclusion if hemodynamically tolerated based on a protocolized hemodynamic protocol aiming to adjust UF_NET_ based on cardiac output, arterial lactate concentration, and preload dependence assessment by postural maneuvers, performed regularly during nursing rounds, and in case of a hemodynamic instability episode. The primary outcome of the study will be the cumulative fluid balance between inclusion and H72 of inclusion. Randomization will be generated using random block sizes and stratified based on fluid overload status at inclusion. The main outcome will be analyzed in the modified intention-to-treat population, defined as all alive patients at H72 of inclusion, based on their initial allocation group.

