### Trial design {8}

The GO NEUTRAL study is a multicenter, open-labeled, randomized, controlled, superiority trial with parallel groups and balanced randomization with a 1:1 ratio. The first version of the protocol was published on March 3, 2021, before the first inclusion (Supplemental Material 1, French version). The WHO Trial Registration Data Set is provided in Supplemental Material 2.

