### Concealment mechanism {16b}

Allocation concealment will be ensured via a central web-based system (Ennov Clinical® 7.5.720). The treatment to which a patient will be allocated will be disclosed only after enrollment in the study.

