## Assignment of interventions: blinding

### Who will be blinded {17a}

Blinding of care providers will be unpracticable as knowledge of the UF_NET_ settings is required to adapt care and apply tested strategies and the hemodynamic protocol. Outcome assessors will not be blinded as group allocation could be deducted from UF_NET_ settings provided in the electronic medical files. Data analysts will be blinded to group allocation, although this may be deducted from the reported fluid balance measurements and applied UF_NET_ rates.

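### The article describes the same randomisation list as having random block sizes and as having a fixed block size; if it is fixed, some allocations in this open-label trial are predictable

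*Protocol article*

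**What the plan says.** The abstract (Methods) reads: "Randomization will be generated using random block sizes and stratified based on fluid overload status at inclusion". Section Sequence generation {16a} reads: "Randomization will be performed in each stratum, with a 1:1 ratio, and using a fixed block size". It continues in the singular: "The block size will only be known by the statistician in charge of the randomization list".

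Other statements bear on how much this matters:

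- **Stratification.** "Allocation sequence will be computer-generated with stratification based on the fluid overload status at the time of enrollment". Centre is not named as a factor, and Study setting {9} gives four ICUs.
- **Blinding.** Trial design {8} describes a "multicenter, open-labeled, randomized, controlled, superiority trial with parallel groups and balanced randomization with a 1:1 ratio". Section {17a} adds: "Blinding of care providers will be unpracticable as knowledge of the UF_NET_ settings is required to adapt care".
- **Concealment.** "Allocation concealment will be ensured via a central web-based system (Ennov Clinical® 7.5.720"; section {16b} says the arm is disclosed only after enrolment.
- **Who enrols.** Under Implementation {16c}, local investigators enrol patients and operate the web system, and only the biostatistician knows the randomisation key.

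**The concern.** Two things are at stake.

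The first is the record. A list has either one block size or several, so the randomisation method is misdescribed in one of the two places, and a trial report that relied on that place would repeat the error.

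The second is conditional on section {16a} being right. Past allocations are visible at the bedside because the ultrafiltration settings reveal the arm. With a constant block size, someone who works out the size and the position in the block knows the allocations that close it. Enrolling clinicians have some room to choose whether and when to enter a patient: eligibility covers the first 24 h of CRRT, and some exclusions rest on judgement, such as expected death within 12 h. In the intervention arm the hemodynamic protocol can halve or stop ultrafiltration, so baseline stability could affect fluid balance. The primary comparison is an unadjusted Mann-Whitney test in patients alive at H72, which would not correct an imbalance introduced at entry.

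**Working it through.** **1. The two statements side by side.** Abstract: several block sizes, chosen at random. Section {16a}: one constant size, then referred to in the singular. Both describe the stratified 1:1 list of this trial, and neither stands in an amendment log. They cannot both be true. The document does not show which list is in the web system.

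**2. Predictability with a fixed block.** The document gives no block size, so sizes 2 to 8 are assumptions. In a balanced block of size 2m, an allocation is certain once all m places of one arm are used. Over all arrangements, the expected share of certain allocations is 1/(m+1).

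Check for size 4 (m = 2): there are 6 arrangements. AABB and BBAA each have 2 certain places; the other four have 1 each. That gives (2×2 + 4×1) / (6×4) = 8/24 = 33.3%.

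| Block size | m | 1/(m+1) |
|---|---|---|
| 2 | 1 | 50% |
| 4 | 2 | 33.3% |
| 6 | 3 | 25% |
| 8 | 4 | 20% |

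**3. Fixed against varying sizes at this trial's size.** Simulation of 58 patients (Sample size {14}) in two strata, with 25% assumed in the fluid-overload stratum. The observer sees every earlier allocation in the stratum and knows the size or the set of sizes.

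| Scheme | Certain allocations |
|---|---|
| Fixed 2 / 4 / 6 / 8 | 49% / 32% / 23% / 18% |
| Varying {2,4} | 11% |
| Varying {4,6} | 6% |
| Varying {2,4,6} | 4% |
| Varying {4,6,8} | 2% |

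The fixed-block figures fall slightly below the formula because the last block in a stratum may be incomplete.

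**4. An observer who sees only part of the list.** The strategy is to guess the arm that is behind so far. Five schemes were simulated: fixed 4, fixed 6, and varying {4,6}, {2,4,6} and {4,6,8}.

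| Share of allocations seen | Correct guesses |
|---|---|
| All | 67% to 70% |
| Half | about 55% |
| A quarter | about 53% |

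Chance is 50%. The rates are nearly the same for fixed and varying blocks. What varying sizes remove is most of the certain allocations, not this simple guessing.

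**5. How much one site might see.** With equal recruitment (an assumption), each ICU contributes 58/(4×2) ≈ 7 patients per stratum on average, interleaved with patients from elsewhere. At the other end, Recruitment {15} reports 12 to 24 patients a year at the coordinating centre in an earlier observational study. If that rate carried over for about two years (an assumption, since eligibility differs), the centre would enrol 24 to 48 of 58, or 41% to 83%.

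**The case against.** The strongest reply is that the safeguards leave little to exploit. The block size is known only to the statistician, the arm appears only after enrolment through a central system, and no stratification by centre is named. A site that sees a quarter to half of the allocations guesses correctly about 53% to 55% of the time, and varying the block size barely changes that. Daily screening of all CRRT patients and the 24 h limit also restrict how long anyone could wait for a preferred slot. This stands, and it makes the percentages in steps 2 and 3 upper bounds. It does not remove the contradiction. Nor does concealing the current assignment prevent inference from past visible ones where one site enrols most of a stratum.

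A reader might go further and infer two things that the documents do not support:

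- **That the primary fluid balance is biased.** No steering is shown. The size of any bias cannot be set against the planned 4000 ml difference, and it is not known that fixed blocks are in use.
- **That the coordinating team can follow all sites and both strata.** The steering committee includes coordinating-centre investigators, meets weekly and verifies compliance. Nothing says that it receives a running list of allocations by stratum.

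**Conclusion.** The contradiction between the abstract and section {16a} is certain and needs correcting whichever statement is true. The predictability concern is conditional on section {16a} being the true one. In that case the upper bound is 50%, 33%, 25% or 20% certain allocations for assumed sizes 2, 4, 6 or 8, against roughly 2% to 11% with the varying schemes examined. These figures assume an observer who knows the scheme and sees the whole stratum. With the stated safeguards and a list apparently shared across four ICUs, the practical risk is modest, and it grows with one site's share of a stratum. This is a correction that should be made. It is not evidence that the trial's result is compromised.

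**What to change.** First have the randomisation statistician confirm which scheme generated the list in use, without disclosing the sizes, and make the abstract and section {16a} agree.

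- **If the list already varies:** correct section {16a} only. The cost is one sentence.
- **If the list is fixed:** correct the abstract, and switch the unused part of the list in each stratum to randomly varying block sizes known only to the statistician. Report the method used for patients already allocated as well as the new one.

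The second route costs more than a text edit. Enrolment is under way in all four centres, and section {25} requires approval of protocol modifications by the ethics committee and the regulatory agency. There is also a slight risk of a small imbalance between arms, because a stratum may end part-way through a block.
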